#### Self-report measures

Subjective cognitive impairment is assessed using the COBRA [59] and CODEL. Quality of life and perceived competence are assessed with the World Health Organization’s Quality-of-Life Assessment (WHOQOL-BREF) [81] and a modified version of the Perceived Competence Scale (PCS) [82], respectively. The user experience in the VR environments is assessed using the following questionnaires: the Presence Questionnaire (PQ) [83, 84], the Multimodal Presence Scale for virtual reality environments (MPS), [85] a modified version of the Technological Acceptance Model (TAM) questionnaire [86], the Virtual Reality Simulation Sickness questionnaire (VRSQ) [87], and a scale comprising items assessing usability and enjoyment composed by our collaborators at the Virtual Learning Lab at the University of Copenhagen. Finally, a user feedback survey has been created by our group to assess participants’ experience and satisfaction with the intervention programme and control treatment.

#### Functional MRI paradigms

During the functional MRI scans, we will administer a spatial N-back working memory task from our previous studies [46, 53] and a word encoding paradigm in which participants must encode and subsequently recognize words of typical household items. The word encoding paradigm was developed in house to capture strategic encoding and memory and exists in two parallel versions that are administered in a counterbalanced design to minimize learning effects.

#### Primary, secondary and tertiary outcomes

For an overview of the frequency and timing of the outcome measures, see Fig. 3. The primary outcome measure is a broad cognitive composite score comprising all five subtasks on the CAVIR test measuring daily life cognitive skills [69]. The secondary key cognitive outcome measure is a domain composite of ‘verbal learning and memory’ comprising the following RAVLT [70] subtests: RAVLT total recall lists I-V, RAVLT immediate recall, and RAVLT delayed recall as we hypothesize that the intervention will specifically improve verbal learning and memory. The secondary outcome measure of daily life functioning is the AMPS [76]. The tertiary (explorative) outcome measures include subtasks on the CAVIR test and individual cognitive domains based on the traditional neuropsychological test battery. Tertiary outcomes of functional capacity, quality of life, and subjective cognitive impairment are UPSA-B [78], FAST [80], WHOQOL-BREF [81], COBRA [59], and CODEL, respectively. The cognitive and functional outcomes are in line with recommendations for cognition trials from the Targeting Cognition Task Force of the ISBD [47]. Specifically, the recommendations are to include a cognitive composite score as the primary outcome, a single key cognitive measure as the secondary outcome combined with an assessment of daily life functioning to investigate possible transfer effects and multiple individual cognition measures as tertiary outcomes [47].

**Fig. 3 Fig3:**
[figure not shown]
Schedule of enrolment, interventions and assessments

### Statistical considerations

#### Primary, secondary and tertiary outcome analyses

To investigate the effect on cognition of VR-based cognitive remediation, data will be analysed using linear mixed models for both primary and secondary outcome measures using the Statistical Package for the Social Sciences (SPSS) version 28. For the primary outcome measure, the dependent variable will be the CAVIR cognitive composite score, which is derived by averaging the five z-transformed subtest scores [69]. Data for neuropsychological tests, level of functioning, subjective cognition, and quality of life will also be analysed using mixed models. Intention-to-treat (ITT) analyses will be performed for missing data using a mixed models approach without any ad hoc imputation [88]. Data will be analysed for every randomized participant for all assessments. Interim analyses will not be conducted given the study’s nature and scale.

#### Functional MRI analyses

fMRI data will be preprocessed and analysed with the FMRIB Expert Analysis Tool (FEAT; latest version available at trial completion) part of FMRIB’s Software Library (FSL; www.fmrib.ox.ac.uk/fsl). fMRI data from the N-back working memory task and the supermarket strategic encoding task will be analysed using a region-of-interest analysis to assess differences between the VR-based cognitive remediation and control groups in neural activity in the dorsal PFC (dPFC) after completing 4 weeks of treatment (adjusting for any difference in neural activity at baseline). We will also conduct volume-of-interest analyses of the dPFC for the N-back task and for both the dPFC and hippocampi for the word encoding task to investigate our hypothesis. Finally, exploratory whole-brain analyses will be conducted to investigate any effects in other brain regions.

#### Sample size and power calculation

The power calculation was performed with the software program G*Power 3.1.9.7 [89]. In the proof of concept of our VR prototype training scenario, we observed a 0.6-point (z-scores) greater improvement in the CAVIR cognitive composite score (primary outcome measure in the present trial) in the VR training compared with a treatment as usual (TAU) group with a 0.9 SD of the change [44]. The power calculation assumed normally distributed data and used a two-tailed sample *t*-test. Based on these parameters, the power calculation revealed that 27 participants per treatment arm are needed to achieve > 80% power for detection of a similar cognitive improvement of at least 0.6 SD (corresponding to a moderate effect size) in the CAVIR training group vs. the control group at an alpha level of 0.05. To accommodate for an approximately 20% drop-out rate from baseline to treatment completion, we will recruit 66 participants (33 participants per intervention arm) to obtain complete data for a minimum of 54 participants (27 participants per arm).

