**Methods:**

The trial has a randomized, controlled, double-blinded, parallel-group design. We will include 66 symptomatically stable outpatients with mood disorders or psychosis spectrum disorders aged 18–55 years with objective and subjective cognitive impairment. Assessments encompassing a virtual reality test of daily life cognitive skills, neuropsychological testing, measures of daily life functioning, symptom ratings, questionnaires on subjective cognitive complaints, and quality of life are carried out at baseline, after the end of 4 weeks of treatment and at a 3-month follow-up after treatment completion. Functional magnetic resonance imaging scans are performed at baseline and at the end of treatment. The primary outcome is a broad cognitive composite score comprising five subtasks on a novel ecologically valid virtual reality test of daily life cognitive functions. Two complete data sets for 54 patients will provide a power of 80% to detect a clinically relevant between-group difference in the primary outcome. Behavioural data will be analysed using linear mixed models in SPSS, while MRI data will be analysed with the FMRIB Expert Analysis Tool (FEAT). Treatment-related changes in neural activity from baseline to end of treatment will be investigated for the dorsal prefrontal cortex and hippocampus as the regions of interest.

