
Virtual reality (VR) platforms have the potential to overcome these challenges because of their highly engaging and real-life-like format. In VR, users can be immersed in naturalistic and multimodal simulations of cognitively challenging daily life scenarios that are quite like situations that patients may encounter in their daily lives [30–33]. VR thereby provides an ecologically valid method for directly practicing the cognitive strategies that are discussed in therapy in a real-life-like safe setting. Notably, studies of VR and learning have found that fully immersive VR, such as a head mounted display (HMD), has a better effect on learning performance than non-immersive learning approaches and improves knowledge transfer to solve real-world tasks [34–36]. It therefore seems reasonable to assume that VR can enhance bridging between cognitive training and daily life cognitive skills in CR interventions and facilitate greater transfer effects [33]. VR simulations using HMDs also induce an increased feeling of being ‘present’ in the virtual environment by effectively shutting out the physical reality [37, 38]. In educational contexts, an increased feeling of ‘presence’ has been shown to influence engagement in VR users by boosting interest and motivation [39]. Similar effects in CR programmes using gamified VR platforms could help instil greater motivation in patients and increase treatment adherence. A recent systematic review found initial promising evidence for the use of fully immersive VR-based cognitive training in neuropsychiatric disorders, particularly if training is relevant for daily life challenges [40]. However, cognitive intervention studies in MD and PSD using VR are still scarce and suffer from various methodological challenges, including a lack of active control groups, small sample sizes, and poor descriptions of intervention components [40–43]. To address this gap, our research group developed a fully immersive VR prototype training scenario in a virtual kitchen environment with input from individuals with MD or PSD in line with recommendations to include expert-by-experience knowledge [44, 45]. We then conducted a randomized, controlled proof-of-concept study in 40 participants with MD or PSD in which the active group trained various cognitive strategies in the VR protype training scenario [44]. This study demonstrated that short-term (1 week), intensive VR-based cognition training had the potential to improve some aspects of cognitive performance [44]. Participants also rated the VR prototype scenario as being a fun, engaging, and safe training environment that felt relevant for their daily lives [44].

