### Virtual reality control treatment

Participants in the control group attend a weekly 2-h session with a therapist during which they complete different VR games that are available through the Oculus Quest games store [68]. The chosen games involve no direct training of cognitive skills, such as planning skills or strategic learning, but merely involve simple reaction time and interaction with an entertaining environment that is meaningful to the participant. At the session, participants also complete alternative versions of the same VR training scenarios as the training group (i.e. kitchen, supermarket, restaurant, and office) in which the training elements (i.e. strategies, adaptive difficulty level, and feedback) have been removed. These control sessions are conducted for three reasons: (i) to assess whether a potential effect on the VR cognition test (primary outcome measure; see details below) reflects a therapeutic effect rather than simple perceptual habituation to VR environments (i.e. becoming better at using and interacting with VR), (ii) to control for the nonspecific effects of meeting weekly with a therapist, and (iii) to blind study participants in both groups so that all participants have the impression of training their cognitive functions and daily life cognitive skills in VR. To ensure engagement in the control group, participants are asked at the end of each session to complete questionnaires evaluating their experiences with the VR games and scenarios.

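### The protocol does not justify carrying the 0.6-point pilot difference, seen against treatment as usual, over to an active VR control, so the stated power of more than 80% has no basis for the contrast tested

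*Protocol article*

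**What the plan says.** The protocol article's section on sample size and power reports the pilot result: "we observed a 0.6-point (z-scores) greater improvement in the CAVIR cognitive composite score", observed "in the VR training compared with a treatment as usual (TAU) group with a 0.9 SD of the change". The calculation is for a t-test at alpha 0.05, with its sidedness stated: "The power calculation assumed normally distributed data and used a two-tailed sample". It concludes that 27 completers per arm are enough, at power above 80%, for "detection of a similar cognitive improvement of at least 0.6 SD (corresponding to a moderate effect size"), where the comparison is between this trial's own two arms. Recruitment is set at 66 to leave 54 with complete data.

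The control in this trial is not treatment as usual. Under the heading on the virtual reality control treatment, controls attend a weekly 2-hour therapist session with VR games, and "participants also complete alternative versions of the same VR training scenarios as the training group", without the strategies, adaptive levels and feedback. Three reasons are given: to tell a therapeutic effect on the primary outcome from habituation to VR, to control for therapist contact, and to blind participants.

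The abstract says that 54 complete patients give 80% power "to detect a clinically relevant between-group difference in the primary outcome". The Background sums up the pilot (40 participants, one week of training) more cautiously: the training "had the potential to improve some aspects of cognitive performance".

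**The concern.** A difference from treatment as usual can include gains from getting used to VR and from seeing a therapist. The control in this trial is designed to take account of both. The pilot difference and the difference tested here are therefore different quantities, and a value for one needs an argument before it serves as the planning value for the other. The protocol gives none, and it reports no result against an active VR control.

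The abstract adds to the difficulty. Calling the target clinically relevant implies a threshold of importance on the CAVIR composite, but the sample-size section derives the target only from the pilot. The protocol does cite such a threshold for the AMPS (0.3 logit), and none for CAVIR.

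At stake is how the primary result will be read. Someone who accepts 80% power for a clinically relevant difference may take a non-significant result as good evidence that no such difference exists. The design does not support that reading.

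**Working it through.** **Inputs.** From the sample-size section: difference 0.6 z-score points, SD of change 0.9, two-sided t-test, alpha 0.05, 27 per arm. From the randomization section: 1:1 allocation. The protocol gives no effect against the active control, so any value other than 0.6 is an assumption, shown as a range.

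**Step 1: the plan's own figure.** Standardized effect d = 0.6/0.9 = 0.667. With n per arm, the noncentrality is d × √(n/2) and the degrees of freedom are 2n − 2. For n = 27 this is 0.667 × √13.5 = 2.45 on 52 degrees of freedom.

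- Two-sided exact-t power at 27 per arm is 67% (69% by the normal approximation), not more than 80%.
- 80% power needs 37 completers per arm (36 by the normal approximation).
- With all 33 per arm and no dropout, power is 76%.
- If 0.6 SD is taken literally (d = 0.6), power at 27 is 58%, and 45 per arm are needed.
- A one-sided test with d = 0.667 comes closest (29 per arm; 78% at 27), but the text says two-tailed.

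The stated figure is not reproduced from its stated inputs.

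**Step 2: power over a range of differences from the active control.** Same formula, SD 0.9, 27 per arm, two-sided 0.05:

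| True difference | d | Power | Completers per arm for 80% |
|---|---|---|---|
| 0.7 | 0.778 | 80% | 27 |
| 0.6 | 0.667 | 67% | 37 |
| 0.5 | 0.556 | 52% | 52 |
| 0.4 | 0.444 | 36% | 81 |
| 0.3 | 0.333 | 23% | 143 |

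Solving for 80% power at 27 per arm gives d = 0.777, a difference of 0.777 × 0.9 = 0.70.

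**Step 3: precision of the pilot value.** Assuming that the 40 pilot participants were split equally, SE = 0.9 × √(2/20) = 0.285. The 95% CI is 0.6 ± 2.024 × 0.285, about 0.02 to 1.18. The pilot is compatible with every row of the table.

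**Step 4: expected precision of this trial.** SE = 0.9 × √(2/27) = 0.245. The 95% CI half-width is about 2.007 × 0.245 = 0.49 points.

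**Step 5: which way the change of setting pushes the effect.**

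- *Downward:* controls do VR kitchen tasks that the protocol says have subtasks similar to those of the CAVIR test. They also meet a therapist weekly.
- *Upward:* the pilot lasted one week, and the participant-retention section likens it to two sessions (60 min) with one scenario. This programme has eight 2-hour sessions over four weeks, four scenarios and home VR training. Controls have one session a week against two, and no home VR training is described for them.

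The protocol does not weigh these against each other.

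**The case against.** The strongest reply is that power is always conditional on a chosen difference. A sponsor may choose 0.6 against an active control wherever the number came from, and the source is stated openly. That is right as far as it goes: the fault lies in the missing justification, not in concealment or in the choice of comparator. The active control is a strength and should stay.

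Three stronger readings are tempting, and the documents do not support them.

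- *That the plan itself expects part of the 0.6 to disappear.* The control section says only that the control helps to interpret an effect, should one be seen. It predicts nothing about size.
- *That the pilot's comparator had no VR exposure.* The article says only treatment as usual. The pilot outcome was change on CAVIR, itself an immersive VR test, so those participants met VR at least through testing.
- *That the true effect here must be smaller.* The longer, broader programme and the only partly matched control contact could enlarge it. The lower rows of the table are assumed values, not estimates.

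Nor can it be said that the trial will probably miss a useful effect, because the protocol defines no useful difference on the CAVIR composite.

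Finally, interpretation rules often belong in an analysis plan, and the article already foresees publishing inconclusive results. So their absence is no fault. The stated power and the wording of the abstract are in this document and can be judged as they stand.

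**Conclusion.** The point holds in this form: the 0.6-point difference is carried from a treatment-as-usual contrast to an active VR control without justification, and nothing supports calling it clinically relevant. The net direction of the error in 0.6 is unknown.

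The stated power therefore has no basis for the contrast tested. It also fails on its own inputs, at about 67% instead of more than 80%. These are separate faults. Raising the number of completers to 37 per arm would cure the arithmetic and still leave the trial powered for a difference seen against another comparator. With 27 per arm, 80% power requires a true difference of about 0.70 points, above the pilot value.

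The figures rest on an SD of change of 0.9 holding in this trial and on the protocol's own t-test. The planned mixed model may be somewhat more efficient, but the protocol gives no correlation from which to quantify that.

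**What to change.** In the sample-size section:

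- say that the pilot's comparator was treatment as usual whereas this trial's is an active VR control;
- either argue why 0.6 is reasonable against that control or present it as an assumption;
- replace the single power figure with two-sided power at 27 per arm over a range: 0.3, 23%; 0.4, 36%; 0.5, 52%; 0.6, 67%; 0.7, 80%.

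In the abstract, restate the 80% and either justify the description of the target as clinically relevant or remove it.

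Interpret the primary result by its estimate and 95% CI (expected half-width about 0.49 points). Do not use 0.6 as the benchmark for declaring no effect. An estimate of 0.10, for example, would have a CI of about −0.39 to 0.59, which excludes 0.6 but still contains differences of 0.3 to 0.5.

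The sample size, design and analysis are unchanged. The cost is wording and a less favourable stated power.

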### Randomization and blinding

The study has a double-blinded design. Neither the participant nor the outcome assessors will know whether the participant is receiving VR-based cognitive remediation or VR control treatment (details below). At inclusion, participants are informed that they will be randomized to one of two types of VR training programmes which both involve weekly sessions with a therapist. To uphold the blinding, participants are not provided with any further details regarding the VR-based cognitive remediation and control treatment until after randomization. Participants are randomized upon full completion of the baseline assessment with allocation being carried out by the first author using the automated randomization module in the online Research Electronic Data Capture (REDcap) system based on an uploaded blocked randomization list created online using Sealed Envelope Ltd. 2022 [64]. Participants will be randomized using a 1:1 allocation in blocks of varying size from 4-8, and we will stratify randomization with age (< or ≥ 35 years) and diagnosis (MD vs. PSD) to ensure equal distribution in the two groups. To avoid any predictability in the randomization process, the list detailing the randomized blocking sequences is kept inaccessible to the first author who enroll and randomize the participants. The participants will be instructed not to disclose any information concerning their treatment during outcome assessments and under no circumstances will the allocation be revealed to the outcome assessors. Outcome assessors will be asked to note whether the blinding was compromised during the assessment. The first author who undertakes the statistical analyses will be blinded with respect to group assignments when conducting the primary and secondary outcome analyses.

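### 27 per arm gives about 67% power on the plan's own inputs, not the stated more than 80%

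*Protocol article*

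**What the plan says.** The calculation is in the Protocol article, Statistical considerations, Sample size and power calculation. It starts from the proof-of-concept study: "we observed a 0.6-point (z-scores) greater improvement in the CAVIR cognitive composite score" than under treatment as usual, "with a 0.9 SD of the change". On the test it says: "The power calculation assumed normally distributed data and used a two-tailed sample" t-test. The significance level is set "at an alpha level of 0.05". From these parameters it states that "the power calculation revealed that 27 participants per treatment arm are needed to achieve" more than 80% power for "detection of a similar cognitive improvement of at least 0.6 SD (corresponding to a moderate effect size"). It then recruits 66 (33 per arm) so that at least 54 (27 per arm) have complete data after roughly 20% drop-out.

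The abstract repeats the claim: "Two complete data sets for 54 patients will provide a power of 80" per cent for a clinically relevant difference in the primary outcome. Under Randomization and blinding, allocation is 1:1.

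**The concern.** Every input that a two-sample power calculation needs is printed, and the text says that 27 per arm follows from them. A difference of two-thirds of an SD usually needs well over 30 per arm for 80% power two-sided, so 27 looked too small.

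The target is also described in two ways, as 0.6 points with an SD of 0.9 and as 0.6 SD. If the second is a standardised effect, the two disagree, because 0.6 points is 0.667 SD.

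This is the power claim for the primary outcome. If it is too high, a non-significant result will look like better evidence against a 0.6-point effect than it is.

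**Working it through.** **Inputs, all from the protocol.** Difference 0.6 points; SD of change 0.9; two-tailed t-test; alpha 0.05; 1:1 allocation; 27 complete per arm (33 randomised per arm).

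**Method.** Two independent samples, noncentral t distribution:

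- d = difference / SD
- noncentrality = d × √(n/2), with n per arm
- degrees of freedom = 2n − 2
- power = probability that |t| exceeds the two-sided 5% critical value

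**Attempt to reproduce the stated figure.**

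- d = 0.6 / 0.9 = 0.667
- noncentrality = 0.667 × √(27/2) = 2.449
- degrees of freedom = 52; critical value = 2.007
- power = 67.2%

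The usual normal approximation gives 68.8%. Neither reaches 80%.

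**Sample size for 80%.** At d = 0.667, 36 per arm gives 79.7% and 37 gives 80.8%. So 37 per arm (74 complete) are needed, 10 per arm more than stated.

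**Other readings that might give 27.**

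| Reading | Power at 27 per arm | n per arm for 80% |
|---|---|---|
| As stated: d = 0.667, two-tailed | 67.2% | 37 |
| 0.6 SD taken as d = 0.60, two-tailed | 58.1% | 45 |
| d = 0.667, one-tailed | 78.0% | 29 |
| d = 0.60, one-tailed | 70.2% | 36 |

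A paired or one-sample t-test needs 20 observations at d = 0.667 or 24 at d = 0.60, so it does not give 27 either.

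**No drop-out.** With all 33 per arm retained, two-tailed power is 76.0% at d = 0.667 and 67.0% at d = 0.60.

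**What 27 per arm can detect.** The smallest d with 80% two-tailed power is 0.777, which is 0.777 × 0.9 = 0.70 points. Put the other way, for 0.6 points the SD of change would have to be 0.6 / 0.777 = 0.77 rather than 0.9.

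**Rounding of the inputs.** The inputs carry one decimal. At the unfavourable limits (0.55 and 0.95), power at 27 per arm is 55% and 48 per arm are needed. At the favourable limits (0.65 and 0.85), power is 79% and 28 per arm are needed. Even the best corner misses the claim.

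**Baseline adjustment.** Suppose that the final model adjusts for baseline, that the SD is the same at both visits, and that r is the baseline-to-follow-up correlation. The variance of change is then 2σ²(1 − r) and the adjusted residual variance is σ²(1 − r²). Their ratio is (1 + r)/2, so the effective d is 0.667 / √((1 + r)/2). The protocol gives no r, so the values below are assumptions.

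| Assumed r | Effective d | Power at 27 per arm |
|---|---|---|
| 0.3 | 0.827 | 85% |
| 0.4 | 0.797 | 82% |
| 0.5 | 0.770 | 79% |
| 0.6 | 0.745 | 77% |
| 0.7 | 0.723 | 74% |

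Power reaches 80% where (1 + r)/2 = (0.667/0.777)², that is at r of about 0.47, and exceeds it only below that.

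**The case against.** The strongest reply is that the primary analysis is a linear mixed model on every randomised participant, not a t-test of change in completers. If that model adjusts for baseline, the true power may be near or above 80%, as the last table shows. This stands in part: 67% is the power of the calculation the protocol describes, and the planned analysis may do better. But the protocol derives its figure from a t-test, gives no correlation, and does not say in this article how baseline enters the model. The reply therefore offers another route to a similar number and does not support the printed derivation.

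Second, the 0.6 SD may simply mean 0.6 z-score units, since the composite averages z-transformed subtests. That is plausible, and the 58% and 45-per-arm figures should then be set aside. It leads back to d = 0.667 and 67%.

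Third, the software may have been set to one tail. That would nearly explain 27, but it is a guess, it contradicts the stated two-tailed test, and 78% is still not above 80%.

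Fourth, nothing in the protocol says that a null result will be judged against the 80% figure. That is true; the risk lies with readers who take the abstract at its word.

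The allowance for drop-out is not in dispute: 54 of 66 is an 18% loss, consistent with roughly 20%.

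**Conclusion.** The concern holds. On the protocol's stated inputs and test, 27 per arm has about 67% power, 13 percentage points below the claim, and 80% needs 37 per arm. If the true difference is 0.6 points with SD 0.9, a two-sided t-test of change in 54 completers misses it about one time in three, not one in five. No two-sided reading of the printed inputs, including full retention at 33 per arm with those inputs or the most favourable rounding at 27 per arm, supports the stated figure.

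This rests on a two-sample comparison of change scores with equal arms, as the protocol describes. The power of a baseline-adjusted mixed model could be higher, but it cannot be known without the correlation. Because the wrong figure concerns the primary outcome and also stands in the abstract, it should be corrected.

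**What to change.** Keep 66 randomised and correct the statement in both the sample-size section and the abstract. Either of these would do:

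- **Keep the t-test basis.** State that 27 per arm gives about 67% power for a 0.6-point difference with an SD of change of 0.9 (two-sided alpha 0.05), or 80% power for 0.70 points.
- **Move to the analysis model.** If the primary model adjusts for baseline, say so, state the assumed baseline-to-follow-up correlation and its source, and give the power under that model.

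In either case, replace the 0.6 SD description with 0.6 points (0.67 SD of change), so that points and SD units are not mixed. In the trial report, interpret a non-significant primary result from the confidence interval for the between-group difference and not from the planned power.

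The cost is a few sentences and a less favourable stated power. No extra patients are needed, and the design does not change.
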